## **PROTOCOL SYNOPSIS**

### **Evaluation of late clinical events after drug-eluting versus bare-metal stents in patients at risk:**

#### **BAseI Stent Kosten Effektivitäts Trial – PROspective Validation Examination, Part II (BASKET-PROVE II)**

---

##### **Background:**

Retrospective detailed analyses of long-term BASKET findings identified patients with large DES ( $\geq 3$ mm Stents) as patients at risk for late cardiac death/nonfatal MI. To prove this findings, BP compared 2-year cardiac death/MI rates in patients treated with a 2nd generation BMS (Vision®) versus standard DES (Cypher®) and versus a 2nd generation DES (XienceV®). Results of 2324 included patients with 12 months aspirin/clopidogrel treatment will be available in 2010. In view of new DES with absorbable polymers and new BMS with thin struts and biocompatible polymers, BP-II will be launched to test their comparative clinical safety up to 5 years if treated with an aspirin/prasugrel combination, since prasugrel halved stent thrombosis rates compared to clopidogrel in a large ACS trial.

##### **Aims :**

- Primary aim: To compare 24 month safety (cardiac death/MI rates) of a new type BMS (P with thin cobalt-chromium struts and biocompatible polymer) in a 1:2 randomisation to two new types of DES (X: durable polymer, low dose –limus drug; N: biodegradable polymer with –limus drug) in unselected patients at low risk for restenosis ( $> 3$ mm stents only) on the background of contemporary antiplatelet therapy.
- Secondary aims:
  - a) To compare the efficacy of BMS vs. DES and the combined endpoint of safety and efficacy of the primary comparison (BMS vs. DES)
  - b) To compare safety and efficacy of each of the new DES to that of the BMS, i.e. X vs P and N vs P
  - c) To compare safety and efficacy of the two new DES, i.e. X vs. N
  - d) & e) Historical comparisons with BP : early BMS strategy (Vision® stent with 12 months Clopidogrel) with the new BMS strategy (P with 1 month Prasugrel in elective and 12 months in ACS-patients); Safety and efficacy of the X-stent in similar patient groups receiving an antiplatelet therapy of 12 months Clopidogrel (BP) vs. those receiving 12 month Prasugrel (BP-II)

##### **Set-up:**

Multicenter prospective randomized trial.

##### **Patient inclusion:**

Unselected series of patients in need of large ( $\geq 3$ mm) stents only in native vessels irrespective of clinical indication.

##### **Patient exclusion:**

In-stent restenosis, Left-main disease, cardiogenic shock, planned surgery  $< 12$  months, increased bleeding risk, no compliance expected, History of stroke or TIA.

##### **Randomization:**

By centre using sealed envelopes 1:2 for BMS to DES and 1:1: for the DES subgroups.

##### **Follow-up:**

After 2,3 and 5 years by structured questionnaire.

##### **Statistics:**

A sample size of 800 patients/stent type (753 plus compensation for a withdrawal rate of 5 to 6%) would provide a power of more than 90% to detect, at an alpha level of 0.05 in a two

tailed test, a significant difference between the BMS group and the DES group. This sample size will also allow to detect a significant difference between the BMS and each of the DES groups with a power of 80% at an alpha level of 0.027.

Intention to treat analysis: bivariable group comparisons will be first performed, then time to event will be evaluated both by Kaplan Meier statistics and Cox-regression analysis taking into account influential factors.

#### **Endpoints:**

- 1° end-point = freedom of combination of cardiac death (all death not clearly of extra cardiac origin and documented non-fatal MI after 24 months).
- 2° end-points = non-MI related TVR; MACE = 1° end-point events + non-MI related TVR; 1° end-point events up to 18 months (for comparison with BASKET and BASKET-LATE); stent thrombosis according to the ARC-definitions; components of the 1° end-points; non-cardiac death (total death); major non-CABG bleeding (need for surgery, blood transfusions, cerebral haemorrhages) during dual antiplatelet therapy (up to twelve months); “net clinical benefit” = 1° end-point + bleeding; long-term follow-up after 36 and 60 months; subgroups with diabetes, acute coronary syndrome, ST-elevation MI, need for GP IIb/IIIa inhibitors, lesions >25 mm.
- End-points will be adjudicated by an independent Critical Events Committee (CEC) blinded to the stent type used.

#### **Clinical Relevance:**

If findings of the retrospective analysis of BASKET/BASKET-LATE are verified by the prospective BASKET-PROVE and BASKET-PROVE II trials, then 1st generation DES may no longer be justified in large native vessel stenting. This would reduce the late harm which includes late cardiac death, which is most relevant in view of the >6 million DES implanted per year worldwide today. In addition, it would reduce costs considerably due to the much lower price of BMS vs. DES. If, however, findings do not confirm results of BASKET-LATE then the “late harm” observed there was a “chance” finding and no longer relevant, or to a much lesser degree than postulated in BASKET-LATE. If findings differ between different stent types the results will help define the most safe and effective stent type to treat patients with the need for large vessel stenting. In addition, results of the study will help to understand the mechanisms of late stent thrombosis: if late clinical events related to late stent thrombosis do no longer or to a lesser extent occur with newest generation DES with a bioabsorbable polymer, then late stent thrombosis is most likely due to the polymer and not to the drug or drug-dose used. By the historical comparison of the XienceV® stent-arms of BASKET-PROVEII with BASKET-PROVE, the analysis will provide also the unique chance to test the performance of an up-to-date DES with a dual antiplatelet therapy with Prasugrel versus Clopidogrel in an unselected real-world population. – Thus, these findings should have major impact on the current use of coronary stents and our understanding of possible reasons for late stent thrombosis.

#### **Abbreviations:**

BP = BASKET-PROVE ; BP-II = BASKET-PROVE II  
X = XienceV® = 2nd generation DES with lower “limus”-drug dose.  
N = Nobori® = DES with bioabsorbable polymer and a novel “limus”-drug (biolimus)  
P = PROKinetik Energy® = BMS with thin struts and a biocompatible polymer

# STUDY PROTOCOL

## 1. Background

BASKET was a prospective study to test the cost-effectiveness of drug-eluting stents (DES) versus bare-metal stents (BMS) in a „real-world“ setting, i.e. in all-comers for percutaneous coronary interventions (PCI) irrespective of indication (1). This trial showed that DES (Cypher®, Cordis, Johnson & Johnson, Miami Lakes, Florida, USA or TAXUS®, Boston Scientific Corporation, Natic, Massachusetts, USA, randomized 1:1) were not cost-effective compared to BMS (Vision®, Guidant Corporation, Indianapolis, Indiana, USA, DES:BMS = 2:1 randomization) at an incremental cost-effectiveness ratio to prevent one clinical event of € 18'031 after 6 months or € 53'094 after 18 months (2). In high risk subgroups such as small vessel stenting, multivessel disease, long lesions, multiple stenting and elderly patients, however, DES were more cost-effective or even cost-saving. BASKET-Late Thrombotic Events (BASKET-LATE), a follow-up investigation of clinical events up to 18 months (month 7 to 18) after discontinuation of clopidogrel identified an excess in late cardiac death/non-fatal myocardial infarction (MI) in patients treated with DES compared to those treated with BMS (3), which was true also after 36 months (4). There was a strong indication that these late clinical events were related to late stent thrombosis. These findings were indirectly confirmed by a large registry of patients from Berne and Rotterdam (5) showing a rate of late angiographically documented stent thrombosis of 0,6% per year during the first 3 years of follow-up in patients treated with DES, an effect not seen after BMS stenting.

Predictors of late clinical events in BASKET-LATE were use of glycoprotein IIb/IIIa inhibitors (as measure of acute coronary syndromes or suboptimal PCI results), prior MI and DES use, and in the Berne/Rotterdam registry the only independent predictor of late stent thrombosis was acute coronary syndrome. A more profound analysis of subgroups benefiting from DES was performed based on the overall BASKET/BASKET-LATE data after 18 months (6).

It suggested that patients with small vessel (<3,0 mm) and bypass graft stenting had a highly significant benefit of DES, not only in reduction of target vessel revascularization (TVR), but also in a reduced rate of cardiac death/non-fatal MI. In contrast, data suggested that patients with large native vessel stenting do not seem to benefit from DES and may even have late harm (see Fig.). These findings were confirmed after 36 months (4) and are in accordance with earlier retrospective analyses from different trials showing a particular benefit of DES in small vessels or long lesions (7-11), diabetes mellitus (12-14) and bypass graft stenting (15,16).

In order to prove this hypothesis, BASKET-PROVE (Evaluation of late clinical events after drug-eluting versus bare-metal stents in patients at risk: BASel Stent Kosten Effektivitäts Trial – PROspective Validation Examination) was initiated in 11 centres in Switzerland, Austria, Denmark and Italy in 2007 (17). In this trial a total of 2324 patients in need for large (>3mm stents only) native vessel stenting only were randomised 1:1:1 to either treatment with Cypher-Select® (standard 1st generation DES) versus Vision® (3rd generation cobalt-chromium BMS) versus XienceV® (DES with a lower dose of a “limus” drug, i.e. Everolimus). The results of the primary endpoint (freedom of combination of cardiac death and non-fatal-MI) will be available by summer 2010.

[figure not shown][figure not shown][figure not shown][figure not shown][figure not shown][figure not shown]

Stents <3.0mm or bypass PCI  
n=268 (32%)

Stents ≥3.0mm and no bypasses  
n=558 (68%)

Comparison of bare-metal stents (BMS; blue dotted line) and drug-eluting stents (DES; red continuous line) regarding cardiac survival free of non-fatal myocardial infarction (MI; top), cumulative rate of non-infarct related target vessel revascularisation (TVR; middle), and survival free of major adverse cardiac events (MACE; bottom) in patients treated with small stents <3mm only or with PCI in bypass grafts (left side) and in patients treated with large stents ≥3mm in native vessels (right side).

Reasons for late stent thromboses lay in delayed endothelial healing and hypersensitivity reactions as noted in autopsy (18) and angioscopic (19) studies and it has been speculated whether prolonged dual antiplatelet therapy (Aspirin and Clopidogrel) may prevent these events. Since no clustering of events after clopidogrel discontinuation was noted in BASKET-LATE (3) nor in the Berne/Rotterdam registry (5) and since events occurred on dual (1/4), mono (1/2) or no (1/4) antiplatelet therapy, prolonged dual antiplatelet therapy may not be the definite solution of the problem. However, based on registry data suggesting a marked benefit of prolonged dual antiplatelet therapy in patients with ACS, clopidogrel was recommended for 9-12 months in these patients (20,21). In view of the fact that the main drug effects are observed within the initial 4 weeks after implantation, prolonged duration of drug action of the DES seems not be the reason for these late events. Therefore, the polymer, "carrier" of the drug on the stent which remains on the surface of the stents after total drug release or the initial drug dose may be relevant factors for delayed healing. As a consequence, DES with biodegradable polymers have been introduced with promising results (22). Simultaneously, the effectiveness of BMS could be improved by further reducing strut thickness (23) and introducing biocompatible coatings (24).

Currently prolonged antiplatelet therapy with Aspirin and Clopidogrel is currently recommended by the FDA and ESC-Guidelines for 12 months after DES (Appendix 1). Prasugrel, a novel thienopyridine, has been investigated in patients with ACS and coronary stenting (25). Compared to standard Clopidogrel therapy early and late stent thrombosis could be reduced by approximatively 50% in DES and BMS treated patients. Prasugrel will be on the market in Switzerland and the EU by Summer 2009 and may rapidly replace Clopidogrel in all stent procedures.

## 2. AIMS

These recent findings and analyses are the basis for two relevant questions which will be addressed prospectively in BASKET-PROVE II.

The primary aim will be:

To assess and compare the 24 month safety (cardiac death/MI) of a new type of BMS with new types of DES in patients at low risk of restenosis, i.e. receiving stents of  $\geq 3,0$ mm diameter only, on the background of contemporary antiplatelet therapy.

The new BMS, with thin cobalt-chromium struts and a biocompatible coating (Prokinetik®), will be compared (in a 1:2 randomisation) to two new DES:

- the most widely used 2nd generation DES with a durable polymer and a low dose - limus drug (XienceV®), which was already used in BASKET-PROVE ),
- a DES with a biodegradable polymer and a -limus drug (biolimus) (Nobori®)

The antiplatelet regime will be Aspirin 100mg and Prasugrel 10mg daily for all patients. Based on current recommendations, this will be given for 1 month after BMS in stable patients and for 12 months after DES implantation and after BMS implantation in patients with ACS.

The secondary aims will be:

- A. To compare the efficacy of BMS vs. DES and then the combined endpoint of safety and efficacy of the primary comparison (BMS vs. DES)
- B. To compare safety and efficacy of each of the new DES to that of the BMS, i.e. XienceV® vs Prokinetik® and Nobori® vs Prokinetik® (both, randomized 1:1)
- C. To compare safety and efficacy of the two new DES, i.e. XienceV® vs. Nobori®

There will be also the possibility to compare findings from BASKET-PROVE II with those of the predecessor study BASKET-PROVE. This will have the following additional secondary aims:

D. To compare safety and efficacy of the earlier BMS strategy (Vision® stent with 12 month clopidogrel), as a historical control, with the new BMS strategy (Prokinetik® stent with 1 month Prasugrel in elective patients and 12 months in patients with ACS)

E. To compare safety and efficacy of the the XienceV® stent in similar patient groups (same indications/exclusions, similar sample size) receiving an antiplatelet therapy of 12 month Clopidogrel (BASKET-PROVE) vs. those receiving 12 month Prasugrel (BASKET-PROVE II) in a "historical" control analysis, evaluating also bleeding rates and "net clinical benefit"

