### **3. Patients**

#### **Included will be:**

- all comers, 24 hours a day, 7 days a week, irrespective of indication for PCI
- in need of large ( $\geq 3.0$  mm stents only) native vessel stenting

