#### 4. Study design

BASKET-PROVE II will be a prospective randomized open-label multicenter trial

Randomization will be 2:1 for DES to BMS. The DES group will be sub-randomized 1:1 for XienceV® to Nobori®.

All patients will receive a loading dose of Aspirin (300-500mg) and of Prasugrel (60mg) initially, followed by a maintenance dose of Aspirin 100mg and Prasugrel 10mg daily for 1 month after BMS in elective patients and 12 month after DES implantation and after BMS implantation in patients with ACS as currently recommended. All other treatments will be given according to current guidelines and patient needs (based on local treating physicians prescriptions, see point 6)

[figure not shown]

Patients without emergency intervention will be included in the study after giving written informed consent. Since BASKET-PROVE II is an all-comer, real-world trial, the quality of the trial strongly depends on inclusion of not only elective, but also emergency patients with acute coronary syndrome and myocardial infarction. Since

these patients commonly suffer from acute chest pain and dyspnea and since every minute of time delay would adversely affect prognosis, it is ethically not acceptable to postpone the intervention to obtain written informed consent prior to study inclusion (in accordance with the Swiss federal law on drugs and medical devices [Heilmittelgesetz], Art. 56). Thus, as soon as coronary intervention is planned and the patient fulfils study entry criteria, the patient will be informed about the trial and asked for oral consent by the operator in charge. This will be done in parallel to preparation of material for coronary intervention, guaranteeing no time delay by inclusion of the patient in the study. Oral consent will be documented on the informed consent form by a second medical person not being involved in the trial. Only with oral consent, the patient will be included in the study and will have to give the definitive written informed consent after the PCI-procedure. Baseline PCI consists of the index procedure and of all planned PCI thereafter ("two step").

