## 6. Concomitant Therapy

Concomitant therapy will be

- Aspirin \* 100 mg/day throughout
- statin throughout
- Prasugrel \* :

*Dosage:*                    -10 mg/day in patients  $\leq 75$  years and body weight  $\geq 60$ kg  
                                     - 5 mg/day in patients  $> 75$  years or body weight  $< 60$ kg

*Duration:*                - 12 months after DES or after BMS in patients with ACS

- 1 month after BMS in elective cases

*Loading dose:* - 60mg

*If loaded with*

*Clopidogrel:* - additional loading with Prasugrel \*\*

- other treatments as clinically indicated

(\*after appropriate loading dosages if indicated)

(\*\*: Reasons for additional loading dose with Prasugrel:

- Same and only mode of action for both drugs at the site of the platelet (irreversible block of P2Y12 - ADP-receptor
- Concentration of active metabolite after loading dose 12 times lower with Clopidogrel compared to Prasugrel
- If no additional loading dose: different levels of platelet inhibition for patients with Clopidogrel and Prasugrel in the early phase
- With additional loading dose: same level of platelet inhibition for all patients in the early phase)

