## 8. End-point definitions

1°end-point = freedom of combination of

- cardiac death (all death not clearly of extra cardiac origin)
- documented non-fatal MI (according to the current ESC-guidelines (28))

after 24 months.

2°end-points =

- non-MI related TVR
- major adverse cardiac events (MACE) = 1°end-point events + non-MI related TVR
- 1° end-point events up to 18 months (for comparison with BASKET and BASKET-LATE)
- stent thrombosis according to the ARC-definitions (29)
- components of the 1°end-points
- non-cardiac death, total death
- major non-CABG bleeding (need for surgery, blood transfusions, cerebral haemorrhages) during dual antiplatelet therapy (up to twelve months) – “net clinical benefit” = 1°end-point + bleeding.
- long-term follow-up after 36 and 60 months
- subgroups with
  - diabetes
  - acute coronary syndrome
  - ST-elevation MI
  - need for GP IIb/IIIa inhibitors
  - lesions >25 mm

End-points will be adjudicated by an independent Critical Events Committee (CEC) blinded to the stent type used.

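### Sections 2 and 4 fix prasugrel at 10 mg daily for everyone, but section 6 sets 5 mg daily for patients over 75 years or under 60 kg, who are eligible

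*Protocol*

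**What the plan says.** The prasugrel maintenance dose is stated in three places.

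- **Section 2 (Aims)** gives one dose without exception: "The antiplatelet regime will be Aspirin 100mg and Prasugrel 10mg daily for all patients".
- **Section 4 (Study design)** opens its dosing sentence with "All patients will receive a loading dose of Aspirin (300-500mg) and of Prasugrel (60mg) initially" and continues "followed by a maintenance dose of Aspirin 100mg and Prasugrel 10mg daily for 1 month after BMS in elective patients". It then gives 12 months for drug-eluting stents and for bare-metal stents in acute coronary syndrome. It mentions neither age nor weight.
- **Section 6 (Concomitant Therapy)**, under its dosage entry, reserves the full dose for one group, "10 mg/day in patients $\leq 75$ years and body weight $\geq 60$ kg". It then sets "5 mg/day in patients" who are older than 75 years or weigh less than 60 kg.

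On eligibility, section 3 (Patients) takes "all comers, 24 hours a day, 7 days a week, irrespective of indication for PCI". Its exclusion list has no age or weight limit.

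**The concern.** An eligible patient of 78 years, or one weighing 55 kg, has two incompatible daily doses in the same protocol. No sentence says which section takes precedence.

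The only pointer from section 4 to section 6 is attached to something else: "All other treatments will be given according to current guidelines and patient needs (based on local treating physicians prescriptions, see point 6". It follows the prasugrel sentence but concerns the remaining treatments. Neither fixed-dose statement therefore sends the reader to the reduced dose.

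What is at stake is over-dosing of older and lighter patients relative to the protocol's own rule, and hence bleeding. Bleeding is a declared secondary endpoint: "major non-CABG bleeding (need for surgery, blood transfusions, cerebral haemorrhages) during dual antiplatelet therapy (up to twelve months". It also enters the net clinical benefit endpoint and the historical comparison with the clopidogrel era (secondary aim E). Both need an unambiguous description of the regimen.

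**Working it through.** This is mainly a comparison of texts. The protocol states no figure that needs to be reproduced.

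**Step 1: the dose instructions side by side.**

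| Patient | Section 2 | Section 4 | Section 6 |
|---|---|---|---|
| 75 years or younger and at least 60 kg | 10 mg/day | 10 mg/day | 10 mg/day |
| Over 75 years or under 60 kg | 10 mg/day | 10 mg/day | 5 mg/day |

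The two groups in section 6 are exact complements, so every patient falls into one of them. The three sections agree for the first group and conflict for the second.

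**Step 2: can the second group enrol?** Inclusion is all-comer. The prasugrel-related exclusions in section 3 are a history of stroke or TIA and severe hypersensitivity. The bleeding-related ones are a need for oral anticoagulation, haemorrhagic diathesis and active bleeding disorders. The synopsis adds increased bleeding risk in general terms. None of these removes patients by age or weight. Section 6 also sets a dose for this group, which presupposes that some will be enrolled.

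**Step 3: size of the difference for one affected patient.** Inputs are 10 mg/day (sections 2 and 4), 5 mg/day (section 6) and the treatment durations (the same in all three sections). I take 365 days for 12 months and 30 days for one month.

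- Ratio: 10 / 5 = 2.
- 12 months (any drug-eluting stent, or a bare-metal stent in acute coronary syndrome): 10 × 365 = 3650 mg against 5 × 365 = 1825 mg, a difference of 1825 mg.
- 1 month (bare-metal stent, elective): 10 × 30 = 300 mg against 5 × 30 = 150 mg, a difference of 150 mg.

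These totals cover maintenance only. The 60 mg loading dose is the same in sections 4 and 6.

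**Step 4: effect on the trial's inference.** The section 6 rule depends on age and weight and not on the stent, so it is the same in all three arms. The conflict therefore does not by itself favour either side of the randomised comparison. Neither the event-rate assumptions nor the alpha levels in section 9 depend on it.

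**The case against.** The best defence is that section 6 settles the dose. It is the dedicated dosing text, with cut-offs, durations, loading dose and a rule for patients already loaded with clopidogrel. Section 2 describes the background regimen in one line and is not a prescribing instruction. On that view, two summary sentences leave out an exception that is given in full elsewhere, and a centre would have to ignore the dosing section to go wrong. The cross-reference in section 4, although grammatically about other treatments, does lead a reader of that paragraph to section 6. Some patients at the highest bleeding risk may be excluded anyway. The cumulative doses only restate the factor of 2 and say nothing about bleeding rates.

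Much of this stands. Section 6 is very probably the intended rule, no clinical consequence can be quantified from the protocol, and the trial's inference is not affected. But it does not remove the contradiction. Section 2 does not merely leave out the exception: it says that the dose applies to all patients, which is false if section 6 governs. That section 6 governs is an inference, since no precedence rule is stated. A multicentre trial that enrols emergency patients around the clock should not leave each centre to draw it. Local habit may not help, since section 1 describes prasugrel as a novel drug that was only then reaching the market.

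**Conclusion.** The point holds: sections 2 and 4 are wrong as written for patients over 75 years or under 60 kg. For each such patient the discrepancy is a factor of 2 in the daily maintenance dose. How many patients this concerns cannot be derived from the protocol.

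The conclusion that sections 2 and 4 should change, and not section 6, rests on a judgement: section 6 is the only section with explicit age and weight criteria, and it gives the more cautious dose. The matter should be fixed because it is a safety-relevant dosing instruction. It is not a threat to the primary analysis.

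**What to change.** In sections 2 and 4, replace the fixed dose with: *prasugrel 10 mg daily (5 mg daily in patients >75 years or <60 kg; see section 6)*. In section 2, the phrase extending 10 mg to all patients should go. Add a statement that section 6 governs antiplatelet dosing, and inform the centres before enrolment starts.

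The cost is two sentences of protocol wording, the precedence statement and a note to the centres. Design, sample size and analysis stay as they are.

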#### **Excluded will be patients with**

- in-Stent Restenosis or in-Stent Thrombosis
- bypass graft disease to be stented
- main stem disease to be stented
- cardiogenic shock by clinical assessment (signs of organ hypoperfusion)
- planned surgery within the next 12 months
- oral anticoagulation needed (artificial heart valves, atrial fibrillation) or chronic haemorrhagic diathesis
- active bleeding disorders
- index-PCI = planned PCI of additional lesion
- no FU expected/possible
- History of stroke or TIA (contrindication for prasugrel)
- known severe hypersensitivity reaction to ASS and/or Prasugrel
- no compliance expected / no informed consent given
- enrolled in another study

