## **11. Finances/Insurance**

The stents will be used as clinically indicated and therefore paid by the health insurance. In fact, the rate of the more expensive DES will only be 2/3 in this study,

compared to the average of 85% overall in Switzerland 2007, resulting in reduced overall health care costs.

Follow-up questionnaires and event documentation as well as analyses will be paid by a special study grant.

The study will be planned, conducted, analysed and interpreted entirely independently from industry and will be entirely founded by research grants of the Basel Cardiovascular Research Foundation and the University of Basel. The concomitant medication is provided for free to all patients by the European Alliance of Ely Lilly Europe.

Since no “investigational” devices will be used (all stents are CE marked and freely available on the market in Switzerland and Denmark) this is in fact an observational clinical study only. A special insurance for all included patients in Switzerland, Austria and Germany will be effected with the Zürich insurance-company before enrolment of the first patient.

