## **15. Clinical Relevance**

If findings of the retrospective analysis of BASKET/BASKET-LATE (12) are verified by the prospective BASKET-PROVE and BASKET-PROVE II trials, then the 1st generation DES may no longer be used for large native vessel stenting. This would reduce the late harm related to late stent thrombosis which includes late cardiac death, which is most relevant in view of the >6 million DES implanted per year worldwide today. In addition, it would reduce costs considerably due to the much lower price of BMS vs. DES. If, however, findings do not confirm results of BASKET-LATE then the “late harm” observed there was a “chance” finding and not relevant further, or to a much lesser degree than postulated in BASKET-LATE. If findings differ between different stent types, results will help define the most safe and effective stent type to treat patients in need for large vessel stenting. In addition, results of the study will help to understand mechanisms of late stent thrombosis: if

late clinical events related to late stent thrombosis do no longer or to a lesser extent occur with newest generation DES with a bioabsorbable polymer, then late stent thrombosis is most likely due to the polymer and not to the drug or drug-dose used. By the historical comparison of the XienceV® stent-arms of BASKET-PROVEII with BASKET-PROVE, the analysis will provide also the unique chance to test the performance of the most widely used DES with dual antiplatelet therapy based on Prasugrel versus Clopidogrel in an unselected real-world population. – Thus, these findings should have major impact on the current use of coronary stents and our understanding of possible reasons for late stent thrombosis.

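### Aim E rests its clopidogrel versus prasugrel comparison on identical exclusions across the two trials, yet BASKET-PROVE II has exclusions whose stated reason is prasugrel

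*Protocol*

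**What the plan says.** Section 2 (Aims) sets two historical comparisons with BASKET-PROVE. Aim E contrasts XienceV with 12 months of clopidogrel (BASKET-PROVE) against XienceV with 12 months of prasugrel (BASKET-PROVE II), on safety, efficacy, bleeding and net clinical benefit, "in similar patient groups (same indications/exclusions, similar sample size"). Aim D sets the Vision BMS strategy, "as a historical control, with the new BMS strategy", and says nothing about shared exclusions.

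The exclusion list in section 3 contains "History of stroke or TIA (contrindication for prasugrel") and "known severe hypersensitivity reaction to ASS and/or Prasugrel". The synopsis also lists the stroke/TIA exclusion.

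On the earlier trial, the synopsis background says: "Results of 2324 included patients with 12 months aspirin/clopidogrel treatment will be available in 2010". Section 1 says that BASKET-PROVE "was initiated in 11 centres in Switzerland, Austria, Denmark and Italy in 2007" and refers to a cited design paper. It also expects prasugrel to reach the Swiss and EU markets only by summer 2009.

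Section 15 presents the XienceV comparison as "the unique chance to test the performance of the most widely used DES" under prasugrel versus clopidogrel. Section 10 calls historical comparisons descriptive, but names only those of net clinical benefit.

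**The concern.** Aim E has no randomisation behind it. Its credibility depends on the two XienceV cohorts being comparable, and the parenthesis in section 2 is the protocol's assurance that they are. At least one exclusion in section 3 exists because of prasugrel, the drug that distinguishes the cohorts. Any resulting difference in case mix therefore lines up exactly with the contrast being estimated and would be read as a drug effect.

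The outcomes named in aim E are the exposed ones: cardiac death/MI, major bleeding (which by the section 8 definition counts cerebral haemorrhage) and net clinical benefit, which combines the two. Aim D makes no claim of sameness, but its BMS cohorts would share the same eligibility difference.

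**Working it through.** The protocol states no figure for this point, so there is none to reproduce. The check has three parts.

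**1. Are the two halves of the parenthesis true?**

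- *Similar sample size.* BASKET-PROVE randomised 2324 patients 1:1:1 (section 1), so 2324 / 3 ≈ 775 per arm. BASKET-PROVE II plans 800 per stent (section 9). The ratio is 800 / 775 ≈ 1.03. This half is correct.
- *Same exclusions.* The stroke/TIA exclusion carries its reason in the text: prasugrel. The hypersensitivity exclusion names prasugrel. BASKET-PROVE started in 2007 on clopidogrel, before prasugrel was expected on the market, so neither reason could have operated there. Whether BASKET-PROVE excluded prior stroke/TIA on some other ground cannot be seen from the protocol. This half is doubtful and can be checked only against BASKET-PROVE's own criteria.

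**2. If BASKET-PROVE admitted these patients, how large is the case-mix effect?**

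Inputs:
- P, the 24-month cardiac death/MI rate in the unrestricted cohort: 10.5% (DES) and 6.0% (BMS), the planning rates in section 9. XienceV is a DES, so 10.5% is the planning base for aim E; 6.0% is the base for aim D.
- q, the share with prior stroke/TIA: assumed 3–10%.
- r, their relative risk of the outcome: assumed 1.5–3.

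The documents give neither q nor r. With no drug effect at all, the rate once these patients are removed is

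p = P / (1 + q(r − 1)), and the apparent risk ratio is 1 / (1 + q(r − 1)).

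| q | r | 1 + q(r − 1) | apparent RR | 10.5% becomes | shift (points) | 6.0% becomes | shift (points) |
|---|---|---|---|---|---|---|---|
| any | 1 | 1.000 | 1.000 | 10.50% | 0 | 6.00% | 0 |
| 3% | 1.5 | 1.015 | 0.985 | 10.34% | 0.16 | 5.91% | 0.09 |
| 5% | 2 | 1.050 | 0.952 | 10.00% | 0.50 | 5.71% | 0.29 |
| 10% | 3 | 1.200 | 0.833 | 8.75% | 1.75 | 5.00% | 1.00 |

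The range is therefore about 0.1 to 1.75 points, with apparent risk ratios from 0.985 to 0.833. The top of the range needs the highest prevalence, the highest relative risk and the highest base rate together. The protocol gives no bleeding rate, so no size is offered for bleeding or net clinical benefit.

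**3. Could a shift of this kind produce a significant result by itself?**

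With 775 versus 800 patients and a two-sided 0.05 test, the power to detect a risk ratio of 0.9 is about 7% at a base of 6.0% and 10% at 10.5%. It would seldom create significance alone. It would still bias the reported estimate.

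**The case against.** The strongest objection is that BASKET-PROVE's criteria are not in the protocol. A reader might infer that BASKET-PROVE II added the stroke/TIA exclusion and that the clopidogrel cohort keeps those patients. The text shows only that the prasugrel rationale could not have applied in 2007; such patients might have been excluded for another reason. This stands, and the point is conditional on the sponsor's check.

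Second, the parenthesis in aim E can be read as describing how the compared groups will be chosen. On that reading it already calls for a restricted cohort, and the fault is unclear wording. This is possible, but no restriction is written anywhere, and the same edit would resolve it.

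Third, the protocol already limits these analyses. It introduces them as a possibility, gives them no alpha or power, makes net clinical benefit descriptive and plans multivariable Cox regression. This lowers the stakes. However, the descriptive label does not name safety, efficacy or bleeding, and a descriptive estimate can still be biased. Cox adjustment deals with this difference only if prior stroke/TIA is among the covariates. The choice of covariates may properly sit in the analysis plan, but the statement of identical exclusions is the protocol's own.

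Fourth, a reader might also infer a different country mix, since section 11 arranges insurance for "included patients in Switzerland, Austria and Germany" while section 1 names Italy for BASKET-PROVE. An insurance sentence is not a list of sites. It omits Denmark, although the same section refers to stent availability there. The documents do not support a country argument.

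**Conclusion.** The point holds in a limited form. Aim E's statement of identical exclusions does not fit an exclusion list with prasugrel-specific entries when the comparator trial used clopidogrel. Confidence is high on that conflict of wording and only moderate on its consequences.

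Confounding by case mix follows if BASKET-PROVE admitted patients with prior stroke or TIA. It would favour prasugrel if those patients have a higher risk of the outcome. Under the assumed prevalence and relative risk the size is modest: about 0.5 points on a 10.5% rate in the middle case, and at most 1.75.

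It would go too far to say that the comparison is known to favour prasugrel, because direction and size rest on two quantities the documents do not give. It would also be wrong to say that aim D claims the same exclusions. The randomised comparisons (the primary aim and aims A to C) are unaffected. This is worth correcting in a stated secondary aim that section 15 puts forward as a test of one drug against the other.

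**What to change.** 1. Check BASKET-PROVE's exclusion criteria against section 3. In section 2, replace the statement of identical indications and exclusions with a list of the actual eligibility differences.
2. For aims D and E, restrict the BASKET-PROVE patients to those who meet the BASKET-PROVE II entry criteria, where the necessary data were recorded. Section 10 says data are collected in analogy to the earlier trial, under broad headings such as history and comorbidities. It does not show that prior stroke/TIA was captured. If it was not, state the limitation.
3. Adjust the historical comparisons for baseline variables recorded in both trials.
4. In section 10, extend the descriptive label from net clinical benefit to all historical comparisons, and bring section 15 into line.

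The cost is protocol wording, a filter and covariates in the historical analyses. Eligibility and treatment do not change and no further patients are needed. The downside is a slightly smaller historical cohort: at 3–10% of about 775, some 23 to 78 patients per arm, leaving roughly 700 to 750.
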